## Data collection and management

### Data management {19}

Data will be kept and anonymized by the principal investigator.

### Confidentiality {27}

The principal investigator will be the only person that will manage the subject’s identification information. All other persons will manage limited and anonymized information.

## Statistical methods

### Statistical methods for primary and secondary outcomes {20a}

A descriptive analysis of the collected values of the variables under study will be carried out, studying the measures of central tendency. Normal distributions will show mean and standard deviation and median and interquartile range in case of non-observation of normal distribution. The normality of the samples will be verified with the Kolmogorov-Smirnov test.

The verification of the hypothesis under study will be assessed using Student’s *T* test for independent samples in case of normality of the sample and by the *U* Mann-Whitney test otherwise.

A multiple linear regression analysis will be performed: considering as a dependent variable the intracranial pressure differences, difference or gain of expiratory flow and between the covariates, the type of technique, the pressure applied in the technique under study, the type of brain injury, blood gases changes, age, and sex.

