**Discussion:**

The safety of chest physiotherapy techniques in patients at risk of intracranial hyperpressure is still uncertain. The aim of this study is to identify if the rapid manual chest compression technique is safe in ventilated patients with acute brain injury.

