### Objectives {7}

#### Main hypothesis

H0—The rapid chest compression technique does not produce a change in intracranial pressure in patients on invasive mechanical ventilation with severe acute brain injury.

H1—The rapid chest compression technique produces changes in intracranial pressure in patients on invasive mechanical ventilation with severe acute brain injury.

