### Sample size {14}

To obtain the sample size needed for this study we worked with the software Ene 3.0 and based the estimations on the changes in intracranial pressure with the techniques performed in the study by Thiesen et al. (2005), in which the mean of baseline measures (equivalent to the control group) was 6.9 mmHg, mean in the experimental group was 7.2 mmHg 30 mins post-physiotherapy and joint standard deviation was 2.0 mmHg in patients with ICP 0–10 mm and the mean of baseline measures (equivalent to the control group) was 13.7 mmHg, mean in the experimental group was 12.7 mmHg 30 mins post-physiotherapy and joint standard deviation was 2.5 mmHg in patients with ICP 10–20 mmHg.

With a power of 80% and to detect that the difference of means is equal to the equivalence limit by means of a *T*-Student test for two independent samples, assuming that the equivalence limit is 2.0 mmHg and a level of confidence of 95%, we obtained a sample size of 25 patients in each group: control and experimental. The total number is 50 subjects for this RCT.

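### The sample size rests on a 2.0 mmHg equivalence limit, but the planned test never uses it, so a non-significant result would not show that the technique is safe

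*Protocol article*

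**What the plan says.** Four places in the protocol article bear on this.

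- **Abstract, Discussion.** "The aim of this study is to identify if the rapid manual chest compression technique is safe in ventilated patients". The main Discussion adds the investigators' belief that the technique, adequately applied, is safe.
- **Sample size {14}.** The calculation is framed as equivalence and names a two-sample t test: "With a power of 80% and to detect that the difference of means is equal to the equivalence limit". The margin and the resulting size of each arm come next: "assuming that the equivalence limit is 2.0 mmHg and a level of confidence of 95%, we obtained a sample size of 25 patients". An earlier uncontrolled study supplies an SD of 2.0 mmHg for baseline ICP of 0–10 mmHg and 2.5 mmHg for 10–20 mmHg.
- **Objectives {7}, Main hypothesis.** The null is: "The rapid chest compression technique does not produce a change in intracranial pressure in patients on invasive mechanical ventilation". The alternative is that it does. Neither carries a margin.
- **Statistical methods {20a}.** Normality is checked by Kolmogorov-Smirnov. The hypothesis is then tested by Student's t "test for independent samples in case of normality of the sample and by the" Mann-Whitney U test otherwise. The section sets no confidence interval or test against 2.0 mmHg.

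**The concern.** The three parts of the primary analysis do not fit together. The sample size speaks of equivalence within a limit, the hypotheses speak of any difference from zero, and the test addresses only the second. Under that test a result is either evidence of a change or an absence of such evidence, so the only result that could favour safety is the absence. That absence can come from a small effect, but equally from noise, few patients or interventions stopped early.

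False reassurance is the costly error. The protocol's own background says that a rise in ICP can lower cerebral perfusion and may worsen haemorrhagic lesions.

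A lesser point is that a pretest chooses the primary test. The p-value of the U test does not address a limit placed on the difference of means, so the data would decide whether the primary result relates to the quantity used in the sample size.

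**Working it through.** **Inputs.** From Sample size {14}: limit 2.0 mmHg, 80% power, 95% confidence (one- or two-sided is not stated), SD 2.0 or 2.5 mmHg, 25 per group. Assumed here: normal data, equal SD in both groups, no missing data.

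**1. Reproduce the stated number.** For an ordinary two-sided difference test,

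n per group = 2 × [SD × (1.960 + 0.842) / 2.0]².

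- SD 2.5: 2 × (3.502)² = 24.5, so 25. This matches the protocol.
- SD 2.0: 15.7, so 16. This does not match.

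SD 2.5 is therefore the base case. The same arithmetic gives a one-sided 2.5% non-inferiority test with a true difference of 0. It is not the sample size for a two-sided equivalence claim.

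**2. The planned test when the true difference equals the limit.**

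- Standard error = 2.5 × √(2/25) = 0.707 mmHg.
- Non-centrality = 2.0 / 0.707 = 2.83 on 48 degrees of freedom.
- Exact t power is 79.1%, so p>0.05 occurs in 20.9% of trials.

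**3. What equivalence would require.** The expected half-width of the interval is t × 0.707, which is 1.19 mmHg (90%) or 1.42 mmHg (95%). For the interval to lie within ±2.0, the observed difference must be within about ±0.81 or ±0.58 mmHg. If the true difference is 0, the approximate chances are:

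- 90% interval: P(|Z| < 0.81/0.707 = 1.15) ≈ 75%.
- 95% interval: P(|Z| < 0.58/0.707 = 0.82) ≈ 59%.

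**4. Side by side.** Simulation with 400,000 trials per row, 25 per group, SD 2.5:

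| True difference (mmHg) | t test p>0.05 | 90% CI inside ±2.0 | 95% CI inside ±2.0 | Share of p>0.05 trials with CI not inside (90% / 95%) |
|---|---|---|---|---|
| 0 | 95.1% | 74.8% | 58.5% | 21.4% / 38.5% |
| 1.0 | 71.7% | 39.5% | 26.7% | 45.0% / 62.8% |
| 2.0 | 20.8% | 4.9% | 2.5% | 76.4% / 88.2% |

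A second run at a true difference of 0 gave 74.6% and 58.2%, hence about 75% and 58%. The 1.0 mmHg row is the size of the shift that {14} quotes for the 10–20 mmHg band (13.7 to 12.7). With SD 2.0, the 20.8% falls to 6.7%, still above the 5% or 2.5% of an equivalence test.

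**5. Numbers for 80% equivalence power.** With SD 2.5 and a true difference of 0, about 28 per group (90% interval) or 34 per group (95% interval). With a true difference of 1.0 mmHg, about 78 or 99 per group.

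**The case against.** The strongest reply is that this is a coherent difference trial with one misplaced word. The objective is to determine effects on ICP, the hypotheses are two-sided, and 25 per group is exactly the difference-test number. The arithmetic part of this stands: the sample size is equivalence in wording only. But the limit, the no-change null and the safety aim all remain in the text, and nothing reconciles them. A separate analysis plan could do so only by departing from {7} and {20a}.

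Several stronger readings are tempting, and the protocol does not support them.

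- **That it plans to report p>0.05 as safe.** No sentence says so. The abstract asks whether the technique is safe, and the Discussion states a belief. The risk is inferred from the aim and the test.
- **That the miss rate at 2.0 mmHg is about 60%.** This needs an SD near 4.1, from mixing the two ICP bands: √[(2.0² + 2.5²)/2 + 3.4²] = 4.08, where 3.4 is half of 13.7 − 6.9. It assumes equal band sizes and a comparison of raw ICP. The protocol gives neither the band sizes nor the SD of change.
- **That Kolmogorov-Smirnov is almost blind at 25 per group.** In simulated skewed (lognormal) samples, the uncorrected test rejected normality in about 2.4%, but the Lilliefors-corrected version in about 41–42%. The protocol does not say which is meant.
- **That Mann-Whitney can never relate to a limit in mmHg.** Under a pure location shift, the matching Hodges-Lehmann interval is in mmHg. Only the p-value fails to address the limit on means.

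**Conclusion.** The point holds and should be fixed before analysis, because the primary conclusion depends on it. The analysis as written cannot deliver an equivalence or safety conclusion, since the limit used for the sample size plays no part in it. The size of the problem is the 21% chance of a non-significant result at a true 2.0 mmHg difference, and the 21% to 39% of non-significant trials that fall short of equivalence even when there is no effect. These figures rest on SD 2.5, normal data and 25 completed patients per group. They would be smaller with a smaller SD of change and larger with a greater one. The normality pretest is secondary and would not merit the same urgency alone.

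**What to change.** Either of two repairs resolves the contradiction.

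**A. Keep the equivalence claim.**

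- Restate the primary hypotheses as H0: the absolute between-group difference in mean ICP change is at least 2.0 mmHg; H1: it is less than 2.0 mmHg.
- Prespecify one between-group mean difference in ICP change with its confidence interval, and state whether it is 90% or 95%.
- Conclude equivalence only if the whole interval lies within ±2.0 mmHg.
- State that p>0.05 on a difference test will not be reported as safety.
- Remove the normality pretest as the selector of the primary test.

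*Cost:* no new measurements, but the stated 80% power no longer applies. At 25 per group, SD 2.5 and a true difference of 0, it becomes about 75% (90% interval) or 58% (95% interval). The investigators must accept that or enlarge the trial. If they decide that only a rise matters, a one-sided 2.5% non-inferiority test against a rise of 2.0 mmHg keeps about 80% at 25 per group.

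**B. Keep the difference test.** Remove the equivalence wording from Sample size {14}, and state that a non-significant result will support no claim of safety.

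*Cost:* wording only, but the trial then gives up the positive safety conclusion that its abstract seeks.

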##### Secondary objectives

Establish a relationship between the type of brain injury and the behavior of intracranial pressure.

Establish a relationship between peak expiratory flow and behavior of intracranial pressure.

Establish a relationship between the pressure applied in the studied technique and the changes in the other dependent variables.

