#### Expiratory and Inspiratory peak flow

Data will be collected in 30 s periods at T−60 m, T−5 m, at the beginning and every minute, T+ 5 m, and T+ 30 m; all expiratory peak flows will be checked and the best will be recorded from every 30 s sequence. Maquet Servo U and I, Hamilton C5 ventilators will be used.

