#### Applied pressure

In order to assure that the technique is performed consistently, the chest compression pressure made by the Physiotherapist will be monitored and data recorded during the procedure application time. The Tekscan ComfortMat 1 will be the device used to measure and record the pressure values (g/cm^2^).

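### The model for gain in expiratory flow does not list starting flow as a covariate, which can cost precision in the technique comparison; the pressure-flow slope should be reported only as an association

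*Protocol article*

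**What the plan says.** Under Statistical methods for primary and secondary outcomes {20a}, the protocol article plans a multiple linear regression for differences in intracranial pressure (ICP) and for the "difference or gain of expiratory flow and between the covariates, the type of technique, the pressure applied in the technique under study", followed by "the type of brain injury, blood gases changes, age, and sex". The patient's flow before treatment is not named.

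That flow is collected. Under Expiratory and Inspiratory peak flow the schedule is "Data will be collected in 30 s periods at T−60 m, T−5 m, at the beginning and every minute, T+ 5 m, and T+ 30" minutes, and for each window "all expiratory peak flows will be checked and the best will be recorded from every 30 s sequence". Two readings therefore clearly precede treatment, at T−60 and T−5.

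Applied pressure is measured and not assigned: "the chest compression pressure made by the Physiotherapist will be monitored and data recorded during the procedure application time". The third secondary objective relies on it: "Establish a relationship between the pressure applied in the studied technique and the changes in the other dependent variables".

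**The concern.** A gain score subtracts the starting value, which fixes its coefficient at exactly 1. If the true regression slope of later flow on starting flow is below 1, the gain still depends on where the patient started, and that dependence stays in the residual. The planned list adjusts for age and sex but not for the starting value of the outcome itself, which is already on file.

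Two results are affected.

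- **Technique effect on flow, both arms.** Randomisation balances starting flow in expectation, so leaving it out causes no bias. The interval may be wider than the data allow.
- **Pressure-flow slope, compression arm.** Pressure is not randomised. If it is related to starting flow or to what lies behind it, the slope may partly reflect which patients were pressed harder.

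The primary ICP comparison is not affected.

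**Working it through.** **The plan's own figure.** The article states a sample size only for ICP. With SD 2.5, difference 2.0, two-sided 5% and 80% power, n = 2 × (1.960 + 0.842)² × 2.5² / 2.0² = 2 × 7.85 × 6.25 / 4 = 24.5, so 25 per group. This matches the article. Nothing below changes it, and no corresponding figure is given for flow.

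**Inputs.** From the article: 25 per group, the dependent variable, the covariate list and the times of the flow readings. Not in the article, hence assumed: r, the correlation of flow before and during treatment (0.3 to 0.9); k, the SD during treatment divided by the SD before; c, the correlation of applied pressure with starting flow (0 to 0.5).

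**1. Technique effect.** With the SD before treatment set to 1, the residual variance is

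- gain alone: 1 + k² − 2rk
- gain with starting flow as a covariate: k²(1 − r²)

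For k = 1 the ratio is (1 − r²) / [2(1 − r)] = (1 + r)/2.

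| r | gain alone | with starting flow | variance ratio | SE of gain alone relative to adjusted |
|---|---|---|---|---|
| 0.3 | 1.40 | 0.91 | 0.65 | 1.24 |
| 0.5 | 1.00 | 0.75 | 0.75 | 1.15 |
| 0.7 | 0.60 | 0.51 | 0.85 | 1.08 |
| 0.9 | 0.20 | 0.19 | 0.95 | 1.03 |

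Estimating one more coefficient in 50 patients raises the adjusted variance by about 47/46, or 2%. The ratios become about 0.66, 0.77, 0.87 and 0.97, and simulation at 25 per arm agrees to within about 0.01.

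For k above 1 the benefit shrinks, and it is nil where rk = 1:

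- r = 0.5, k = 1.5: 1.6875 / 1.75 = 0.96
- r = 0.7, k = 1.4: 0.9996 / 1.00 = 1.00
- r = 0.8, k = 1.25: 0.5625 / 0.5625 = 1.00

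**2. Pressure-flow slope.** Both mechanisms below were simulated with 25 compression patients, k = 1, no true effect of pressure and no other covariates. The entries are rejection rates of a nominal 5% test.

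*Mechanism A: pressure follows the measured starting flow.* Without starting flow in the model, the slope is biased by (r − 1)c flow SDs per SD of pressure; for r = 0.5 and c = 0.5 that is −0.25.

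*Mechanism B: a stable patient trait raises flow equally before and during treatment and also drives pressure.* Subtraction removes the trait. Conditioning on a single noisy reading of it brings the bias back.

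| r | c | A: gain alone | A: with T−5 flow | B: gain alone | B: with T−5 flow |
|---|---|---|---|---|---|
| 0.5 | 0.3 | 11% | 5% | 5% | 14% |
| 0.5 | 0.5 | 23% | 5% | 5% | 36% |
| 0.8 | 0.3 | 7% | 5% | 5% | 8% |
| 0.8 | 0.5 | 12% | 5% | 5% | 15% |

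If c = 0, both models reject in about 5%. The two mechanisms give opposite advice, and the article has nothing to decide between them.

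**The case against.** The strongest reply is that the gain already uses each patient's own starting flow, that the technique effect is unbiased either way, and that the covariate list may be open-ended: the wording can be read as naming some covariates among others, and a separate analysis plan may complete it. The assumption of equal variances can also be doubted. The technique is meant to raise expiratory flow, so flow may well vary more during treatment, and the precision gain could then be close to nil.

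Much of this stands. It makes the point one of efficiency on a secondary outcome and not an error of validity. It does not remove the point. The article fixes the form of the outcome and lists covariates down to age and sex, yet names neither the reading that defines the gain nor that reading as a covariate. In the two-arm comparison the adjustment costs about 2% in variance at worst and saves up to about a third over the range considered.

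A reader might go further and infer that the pressure-flow slope is confounded and that adding T−5 flow would restore a 5% error rate. The article does not support either step. It nowhere links applied pressure to starting flow, body size or chest stiffness, and it says pressure is monitored so that the technique is applied consistently. If stable traits such as body size or chest stiffness do drive pressure and shift flow equally before and during treatment, the gain model holds its 5% level and adding T−5 flow breaks it (mechanism B).

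**Conclusion.** The point holds for precision. Under equal variances, adding starting flow cuts the variance of the randomised technique effect on flow gain by 35% at r = 0.3, 25% at r = 0.5 and 5% at r = 0.9, slightly less once the extra coefficient is counted. The saving shrinks, and can vanish, if flow is more variable during treatment than before. Both r and k are assumptions.

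The absence of bias refers only to leaving out starting flow. It does not vouch for other listed covariates, such as applied pressure and blood-gas changes, which are measured after randomisation.

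The pressure-flow slope is open to confounding because pressure is not randomised, but confounding is not shown, and neither analysis is safe under every plausible mechanism. The sample size and the primary ICP test are unaffected.

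**What to change.** In Statistical methods for primary and secondary outcomes {20a}:

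1. Define the gain in expiratory flow from the T−5 peak expiratory flow. T−5 is preferable to T−60 because the Intracranial pressure section ties the one-hour reading to a change of ventilation mode.
2. Enter T−5 peak expiratory flow as a covariate in the two-arm model for the technique effect on flow gain.
3. Estimate the pressure-flow slope within the compression arm, report it with and without T−5 flow, and call it an association. If the two estimates differ, say so and do not present the adjusted one as corrected.

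The cost is a few sentences and one degree of freedom in the two-arm model. The second version of the slope also uses one degree of freedom among 25 patients. No new data are needed, since the reading is already scheduled.

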### Eligibility criteria {10}

#### Inclusion criteria:

Intubated patients with mechanical ventilation in Volume Controlled, Pressure Controlled and Volume Controlled Pressure Regulated modes during the 48 h prior to the application of the techniqueSevere head injury with a GCS≤8 before sedation or after the surgical procedures, when needed.Hemodynamic stability (MAP> 65 mmHg)Respiratory stability (PEEP <10cmH_2_O and FiO_2_ < 60%)Intracranial Pressure Stability (0 <ICP < 20 mmHg)RASS sedation scale of − 5 pointsInformed consent obtained

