#### Intracranial pressure

The intracranial pressure (mmHg) data will be recorded 1 h prior to the intervention, due to the change in mechanical ventilation mode, 30 min prior, 5 min prior, at the beginning of the intervention and every minute since the beginning, 5 and 30 min since the end with the continuous intracranial pressure monitoring system from Integra® Camino®.

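### Starting ICP is measured three times before the intervention but is not an adjustment covariate in the two-sample test or the regression, which costs precision, substantially so if raw follow-up ICP is compared

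*Protocol article*

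**What the plan says.** The eligibility criteria of the protocol article require "Intracranial Pressure Stability (0 <ICP < 20 mmHg", so the entry range is 20 mmHg wide. The sequence generation section describes a list of 50 subjects in two groups and mentions no stratification by ICP.

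Under the outcome heading for intracranial pressure, ICP is "recorded 1 h prior to the intervention, due to the change in mechanical ventilation mode, 30 min prior, 5 min prior", then at the start, every minute from then on, and 5 and 30 minutes after the end.

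The statistical methods section tests the hypothesis with "Student’s *T* test for independent samples in case of normality of the sample and by the *U* Mann-Whitney test otherwise". Neither test takes a covariate. A multiple linear regression follows, "considering as a dependent variable the intracranial pressure differences, difference or gain of expiratory flow", with the covariates "the type of technique, the pressure applied in the technique under study, the type of brain injury, blood gases changes, age, and sex". Starting ICP is not among them.

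The sample size section quotes results by starting ICP from an earlier study. In the 0–10 mmHg band, "the mean of baseline measures (equivalent to the control group) was 6.9 mmHg", with 7.2 mmHg 30 minutes after physiotherapy and a joint SD of 2.0 mmHg. In the 10–20 mmHg band the baseline mean was 13.7 mmHg, and "mean in the experimental group was 12.7 mmHg 30 mins post-physiotherapy and joint standard deviation was 2.5 mmHg in patients with ICP 10–20 mmHg".

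**The concern.** ICP before the intervention is the obvious predictor of ICP after it, and the protocol's own source figures say so: the follow-up means of the two bands lie 12.7 − 7.2 = 5.5 mmHg apart, nearly three times the 2.0 mmHg limit on which the trial is sized. The covariate list has room for age, sex and two quantities that arise after randomisation (applied pressure and blood gas changes), but not for this one. Because the article names the test and enumerates the covariates, this is a stated choice and not a detail left open for an analysis plan.

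Precision is at stake. With 25 patients per arm, starting ICP can differ noticeably between arms by chance. An unadjusted comparison carries that difference as noise. The sample size calculation, in contrast, uses an SD that applies within a band of starting ICP.

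A smaller matter is the reference reading. The reading at 60 minutes is tied to a change of ventilation mode, and the regression does not say from which reading its ICP differences are taken.

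**Working it through.** **Inputs.** From the sample size section: band means 6.9 → 7.2 and 13.7 → 12.7 mmHg, SDs 2.0 and 2.5 mmHg, difference 2.0 mmHg, power 80%, confidence 95%, 25 per group. Assumptions of this check, not given in the documents: the share w of patients in the lower band (25, 50 or 75%), and that each band's joint SD applies both before and after the intervention.

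**1. The plan's own figure.** For a two-sided two-sample comparison, n = 2 × [2.5 × (1.960 + 0.842) / 2.0]² = 24.5, hence 25 per group. This matches the stated figure (26 with the t distribution). With SD 2.0 the result is 16. So the SD behind the 25 is, on this reading, the within-band 2.5 mmHg.

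**2. Chance imbalance at baseline, w = 50%.**
- Within-band variance: (2.0² + 2.5²)/2 = 5.125.
- Between-band variance: 0.25 × (13.7 − 6.9)² = 0.25 × 6.8² = 11.56.
- Baseline SD: √16.685 = 4.08 mmHg.
- SE of the between-arm baseline difference: 4.08 × √(2/25) = 1.16 mmHg. A difference above 2.0 mmHg in either direction then occurs about 8% of the time.

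**3. How much passes into the result.**
- Slope of follow-up on baseline: 5.5/6.8 = 0.81.
- Slope of change on baseline: (−1.0 − 0.3)/6.8 = −0.19.
- Raw 30-minute ICP: 0.809 × 1.155 = 0.93 mmHg per one-SE imbalance, nearly half of 2.0.
- Change score: 0.191 × 1.155 = 0.22 mmHg, about 11% of 2.0.

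**4. Standard error on raw 30-minute ICP, w = 50%.** The follow-up SD is √(5.125 + 0.25 × 5.5²) = √12.69 = 3.56, which gives an SE of 3.56 × √(2/25) = 1.01 mmHg. Without the between-band part, the SD is √5.125 = 2.26 and the SE 0.64 mmHg.

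**5. Power for a true difference of 2.0 mmHg, two-sided 5%, 25 per arm, raw ICP.** Follow-up variance = w × 2.0² + (1 − w) × 2.5² + w(1 − w) × 5.5².

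| Lower-band share | Overall SD | Unadjusted power, normal (t) | n per arm for 80% | Within-band SD | Power adjusted for band (t) |
|---|---|---|---|---|---|
| 25% | 3.37 | 55% (54%) | 45 | 2.38 | 83% |
| 50% | 3.56 | 51% (49%) | 50 | 2.26 | 86% |
| 75% | 3.20 | 60% (58%) | 41 | 2.14 | 90% |

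**6. If change is tested.** The documents give no baseline-to-follow-up correlation ρ. With SD 2.5 and the 24.5 of step 1, a change score needs 24.5 × 2(1 − ρ) and an analysis of covariance 24.5 × (1 − ρ²) per arm:

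| ρ | Change score | Analysis of covariance |
|---|---|---|
| 0.3 | 35 | 23 |
| 0.5 | 25 | 19 |
| 0.7 | 15 | 13 |

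Adjustment needs fewer patients at each of these values, but the gain over change shrinks as ρ rises.

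**The case against.** The strongest reply is that baseline may already be in the analysis. The hypotheses speak of a change in ICP, and the regression outcome is a difference. If these are pre-to-post differences, baseline enters by subtraction and most of the exposure goes: 0.22 mmHg instead of 0.93. This stands. A reader might infer that baseline ICP is ignored altogether; the text supports only that it is not an adjustment covariate.

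Second, an unadjusted test in a randomised trial is unbiased and keeps its type I error, and chance imbalance is already part of its standard error. This also stands. The loss is one of precision, and it would be wrong to call the planned test invalid.

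Third, one might read the changes of +0.3 and −1.0 mmHg as drift, or regression to the mean, unrelated to treatment. The background section says that the source study had neither a control group nor randomisation, and the protocol gives no source sample size. The figures show that follow-up ICP depends on starting level, not why, and the 0.81 slope rests on two pairs of means.

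Fourth, a reader might infer that the 60-minute reading would bias the trial. The protocol does not say that differences start there, nor whether that reading falls just before or just after the mode change. The schedule does not distinguish the arms, so an effect common to both would cancel in the between-arm comparison. It could add noise, and no more than that is claimed here.

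**Conclusion.** The point holds as one of efficiency. Starting ICP is collected, is strongly related to follow-up ICP in the protocol's own source figures, and is an adjustment covariate in neither stated analysis.

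The size depends on what is compared. For raw 30-minute ICP the loss is large: an SE of about 1.01 instead of 0.64 mmHg at an even band mix, and power of roughly one half to 60% where 80% was planned. For change it is modest. The statistical methods section does not settle which applies.

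All sizes rest on the assumed band mix, on the quoted SDs holding before and after the intervention, and on reading the sample size as a two-sided test of a 2.0 mmHg difference.

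One might conclude that 25 per group is wrong. That does not follow: the figure reproduces with the within-band SD, and an analysis that removes the between-band variation would match it.

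**What to change.** - Make the between-arm comparison of ICP, at a named primary time point, an analysis of covariance with arm and baseline ICP. Define baseline as the mean of the readings 30 and 5 minutes before the intervention.
- State in advance a rank-based or robust version for clearly non-normal residuals, in place of the present choice between the t and Mann-Whitney tests.
- Add the same baseline term to the regression covariates.
- Do not take ICP differences from the 60-minute reading. Keep it to describe what happens around the change of ventilation mode.

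The cost is a change of wording in the statistical methods section and one model term. Every reading is already scheduled and no patients are added. The primary time point has to be fixed for the model to be specified.
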